# A pragmatic, open-label, multi-center, randomized controlled clinical trial on the rotational use of interfaces *vs* standard of care in patients treated with noninvasive positive pressure ventilation for acute hypercapnic respiratory failure: the ROTAtional-USE of interface STUDY (ROTA-USE STUDY)

**DOI:** 10.1186/s13063-023-07560-1

**Published:** 2023-08-13

**Keywords:** Noninvasive ventilation, Hypercapnic acute respiratory failure, Pressure ulcers, Rotational use of interfaces

## Abstract

**Background:**

In the last decades, noninvasive ventilation (NIV) has been increasingly used to support patients with hypercapnic and hypoxemic acute respiratory failure. Pressure ulcers are a frequently observed NIV-related adverse effect, directly related to interface type and exposure time. Switching to a different interface has been proposed as a solution to improve patient comfort. However, large studies investigating the benefit of this strategy are not available. Thus, the aim of the ROTAtional-USE of interface STUDY (ROTA-USE STUDY) is to investigate whether a protocolized rotational use of interfaces during NIV is effective in reducing the incidence of pressure ulcers.

**Methods:**

The ROTA-USE STUDY is a pragmatic, parallel arm, open-label, multicenter, spontaneous, non-profit, randomized controlled trial requiring non-significant risk medical devices, with the aim to determine whether a rotational strategy of NIV interfaces is associated with a lower incidence of pressure ulcers compared to the standard of care. In the intervention group, NIV mask will be randomly chosen and rotated every 6 h. In the control group, mask will be chosen according to the standard of care of the participating centers and changed in case of discomfort or in the presence of new pressure sores. In both groups, the skin underneath the mask will be inspected every 12 h for any possible damage by blinded assessors. The primary outcome is the proportion of patients developing new pressure sores at 36 h from randomization. The secondary outcomes are (i) onset of pressure sores measured at different time points, i.e., 12, 24, 36, 48, 60, 72, 84, and 96 h; (ii) number and stage of pressure sores and comfort measured at 12, 24, 36, 48, 60, 72, 84, and 96 h; and (iii) the economic impact of the protocolized rotational use of interfaces. A sample size of 239 subjects per group (intervention and control) is estimated to detect a 10% absolute difference in the proportion of patients developing pressure sores at 36 h.

**Discussion:**

The development of pressure ulcers is a common side effect of NIV that negatively affects the patients’ comfort and tolerance, often leading to NIV failure and adverse outcomes. The ROTA-USE STUDY will determine whether a protocolized rotational approach can reduce the incidence, number, and severity of pressure ulcers in NIV-treated patients.

**Trial registration:**

ClinicalTrials.gov NCT05513508. Registered on August 24, 2022.

## Administrative information

Note: the numbers in curly brackets in this protocol refer to SPIRIT checklist item numbers. The order of the items has been modified to group similar items (see http://www.equator-network.org/reporting-guidelines/spirit-2013-statement-defining-standard-protocol-items-for-clinical-trials/).

**Table Taba:** 

Title {1}	A pragmatic, open-label, multi-center, randomized controlled clinical trial on the rotational use of interfaces *vs* standard of care in patients treated with noninvasive positive pressure ventilation for acute hypercapnic respiratory failure: the ROTAtional-USE of interface STUDY (ROTA-USE STUDY)
Trial registration {2a and 2b}.	ClinicalTrials.gov identifier: NCT05513508
Protocol version {3}	I version, 1^st^ July 2022 approved by the Ethical Committee of the coordinating center; minor protocol amendment presented on 26^th^ January 2023,was approved by the Ethical Committee on the 21^st^ February 2023.
Funding {4}	This research received no specific grant from any funding agency in the public, commercial or not-for-profit sectors.

## Introduction

### Background and rationale {6a}

In recent years, noninvasive ventilation (NIV) has increasingly become a common approach for the treatment of hypercapnic [1, 2] and hypoxemic [3] patients both inside [3] and outside [4–6] the intensive care unit (ICU). NIV refers to the delivery of a positive pressure to the patient through interfaces like masks or helmets without the need for invasive endotracheal intubation [7]. These interfaces can efficiently and non-invasively support patients with acute respiratory failure (ARF), preserving airway defense mechanisms, speech, and swallowing, averting the need for prolonged sedation, lowering the occurrence of ventilator-associated pneumonia [8], and ultimately reducing ICU admission [9] and mortality [2]. Nonetheless, NIV failure is observed in 8% of hypercapnic [10] and 50% of hypoxemic patients [11], leading to delayed initiation of invasive ventilation treatment and poor outcomes [5, 10, 12, 13].

As patient comfort is a major factor for NIV success [14], the selection of the most suitable interface type is of paramount importance [15]. Another key variable that should be taken into account to achieve patient comfort and avoid the generation of skin breakdown until pressure ulcers, a frequently observed NIV side effect [7], is the time of exposure to a given interface. Indeed, when the pressure applied between the interface and the skin exceeds the capillary pressure, skin breakdown may occur, resulting in NIV discontinuation due to pain and intolerance [16]. Published incidence rates of facial pressure ulcers associated with NIV masks range from 2 to 31% [17–22] depending on the type of mask used, length of treatment, ventilator setting, humidification, nutritional status, and preventative measures adopted.

The development of pressure ulcers is associated with adverse outcomes that may contribute to patient pain and suffering, impaired quality of life [23], and increased hospital costs [24, 25].

Prevention is usually considered the most efficient solution to address pressure ulcers caused by NIV. Recommended preventative measures for skin damage due to pressure, friction, or shear include the following: (1) correct choice of interface and ventilator (2) reducing the time of uninterrupted NIV administration, (3) application of wound care dressing, and (4) absence of humidification. In particular, the interface should be chosen according to size and attachment. On the one hand, it should not be too loose to cause unintentional leakage, which would worsen patient-ventilator interaction. On the other hand, it should not be too tight to increase the risk of skin breakdown.

As for the exposure time to the interface, a previous study assessing the incidence, location, and stage of pressure ulcers in ICU patients requiring NIV for > 24 h showed that the average exposure time for pressure ulcer development ranged from 1.25 to 74 h ( *x̅* = 28.4 h) for oronasal masks and from 24.75 to 98 h (*x̅* = 61.37 h) for total face masks [17, 18]. The ensuing recommendation was that patients receiving NIV for more than 24 h should be switched to different interfaces to improve their comfort and reduce the occurrence of pressure sores [26–28]. In pre-term infants, the rotational use of interfaces has been tested in randomized controlled trials (RCTs) with discordant results [29, 30]. Among adults, the rotational use of interfaces has been proven feasible both in hypoxemic [28] and hypercapnic [27] patients. Routine interface rotation can also be performed during helmet NIV in a percentage that varies between 3 [31] and 30% [28] in a cohort of patients needing continuous NIV for 1 and 4 days, respectively. Of note, 3% of the patients requiring intermittent helmet continuous positive airway pressure (CPAP) due to COVID-19 needed interface rotation during the treatment [5].

Even though interface rotation is generally accepted as a mean to improve NIV tolerance while reducing the risk of pressure sores [32–34], it is not clear when (i.e., before or after the occurrence of pressure sores) and how often the interface should be rotated. Furthermore, the clinical impact of interface rotation on the incidence or severity of pressure sores and comfort as well as its cost-effectiveness are still unknown.

### Objectives {7}

#### Primary objective

To determine if a protocolized rotational use of interfaces during NIV compared to the standard of care is effective in reducing the development of new pressure sores in patients with hypercapnic ARF treated continuously (> 24 h) with NIV administered (i) to avoid intubation (ii) as an alternative to invasive ventilation, (iii) to avoid reintubation after early extubation, or (iv) to prevent reintubation.

### Trial design {8}

The ROTA-USE STUDY is designed as a pragmatic, parallel arm, open-label, multicenter, spontaneous, no-profit, randomized, controlled, trial requiring non-significant risk medical devices. Figure 1 summarizes the research design, the main inclusion and exclusion criteria, and the variables collected.

**Fig. 1 Fig1:**
[figure not shown]
Research design of the study protocol. NIV, noninvasive ventilation; COPD, chronic obstructive pulmonary disease

## Methods: participants, interventions, and outcomes

### Study setting {9}

Data will be collected from ICUs, intermediate respiratory care units, respiratory medicine, or internal medicine services in 23 centers in Italy.

### Eligibility criteria {10}

#### Inclusion criteria

To be eligible for randomization, patients must meet all the following criteria:Age ≥ 18 years old;Patients with chronic obstructive pulmonary disease (COPD) exacerbation or with hypercapnic ARF of a different etiology receiving NIV (i) to avoid intubation (pH < 7.35 with an arterial partial pressure of carbon dioxide (PaCO_2_) > 45 mmHg and an arterial partial pressure of oxygen (PaO_2_) < 65 mmHg at room air plus respiratory rate > 25 breaths/min with clinical signs of respiratory muscle distress) or (ii) as an alternative to invasive ventilation (pH ≤ 7.20 with PaCO_2_ > 45 mmHg and PaO_2_ < 65 mmHg at room air plus respiratory rate > 25 breaths/min with clinical signs of respiratory muscle distress) (iii) to avoid reintubation after early extubation in patients who present the readiness to wean criteria but failed a spontaneous breathing trial or (iv) to prevent reintubation;Patients must be admitted to the ICU, intermediate respiratory care unit, respiratory medicine service, or internal medicine service according to the hospital organization; andTreatment forecast must be greater or equal to 24 h.

#### Exclusion criteria

Patients, on admission, with skin breakdown or non-blanchable erythema in one of the following areas: nasal bridge, nasolabial fold, cheek, or scalp;Patients who refuse to consent to the study protocol;Patient known to be pregnant;Patients with the following contraindications to NIV: lack of spontaneous breathing; gasping; anatomical or functional airway obstruction; gastrointestinal bleeding or ileus; coma; massive agitation; massive retention of secretions despite bronchoscopy and aggressive physiotherapy; hemodynamic instability (e.g., cardiogenic shock, myocardial infarction); status post-upper gastrointestinal surgery;Patients entering the hospital with asthma or cardiogenic pulmonary edema;Patients with tracheostomy;Patients receiving NIV only for palliation of symptoms (e.g., dyspnea relief). These patients belong to category 3 as defined by the Society of Critical Care Medicine (SCCM) Task Force assessing the palliative use of noninvasive positive pressure ventilation [35];Use of high-flow nasal cannula integrated with NIV to prevent reintubation;Pre-existing skin erythematosus disorders;Known hypersensitivity to skin protective devices (i.e., polyurethane films, colloids, foams);More than 2 h of NIV application before randomization;Patients already included in the study protocol at an earlier stage of their hospital stay; andRefuse to wear NIV interface due to comfort.

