### Intervention description {11a}

In the control group, mask will be chosen among the three types of masks available: oronasal, total face, or hybrid mask, according to the standard of care of the participating centers. Patients wearing oronasal masks will receive protective dressing on their nasal bridges before starting NIV. Interface will be changed in case of discomfort, referred by the patient as unbearable, or in the presence of a pressure sore.

In the intervention group, the mask initially applied to the patient will be randomly chosen between the two most used masks in that center among those available (i.e., oronasal, total face, or hybrid mask). Thereafter, NIV mask will be changed every 6 h, alternating the two different interfaces. Patients wearing oronasal masks will receive a protective dressing on the nasal bridge before starting NIV. In case of discomfort, referred by the patient as unbearable related to one of the two interfaces, NIV will be continued with the other mask.

In both arms, the treatment will be continued until patients require NIV according to the assigned protocol.

Prior to patient recruitment, the candidate assessors (doctors and nurses) will be trained to recognize and stage pressure sores through a specific standardized education module. At the end of this course, the trainees will be asked to take a final test where they have to correctly stage 10 pressure sores. Only those trainees able to identify and stage all 10 sores will be qualified as assessors. To minimize detection bias, assessors will not participate in patient care and will be blinded to treatment allocation.

The skin underneath the mask and occipital region will be inspected every 12 h for possible damage by the assessors. If a pressure sore is detected, the physician in charge of the patient will be promptly informed, and a note will be written on the nursing record. Pressure sores will be staged according to the classification of the National Pressure Ulcer Advisory Panel, European Pressure Ulcer Advisory Panel, and Pan Pacific Pressure Injury Alliance [36] (Table 1).

**Table 1 Tab1:** Pressure sores classification according to the classification of the National Pressure Ulcer Advisory Panel, European Pressure Ulcer Advisory Panel, and Pan Pacific Pressure Injury Alliance

Stage I	A reddened, painful area on the skin that does not turn white when pressed. This is a sign that a pressure ulcer may be forming. The skin may be warm, cool, firm, or soft.

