### Outcomes {12}

The primary effectiveness outcome is the proportion of patients developing at least one pressure sore of any stage at 36 h from randomization. The reason why this measure of effectiveness was chosen is that it is more clinically relevant than the overall number of pressure sores. Furthermore, 36 h seems to be an appropriate time point given that the time it takes for pressure sores to develop is extremely variable, but it might as well be very short.

Secondary outcomes will be the onset, number, and stage of pressure sores and comfort during NIV measured at different time points (12, 24, 36, 48, 60, 72, 84, 96 h). At the same time points, the location of pressure sores per patient will also be recorded, i.e., forehead, nose bridge, left cheek, right cheek, chin, left periauricular, right periauricular, and occipital. The study will also monitor the number of patients that interrupts NIV due to discomfort, the presence/absence of eye irritation in relation to both oronasal and full face/hybrid mask, poor adherence to the protocol (e.g., duration of NIV treatment/day, interfaces changed and hygiene protocol application both during each 12-h protocol period) and the presence/absence and types of vasoactive medications, i.e., epinephrine, norepinephrine, vasopressin, dobutamine, dopamine, other. Further outcomes include the costs for intervention implementation (e.g., mask-related costs) and those related to the care of pressure sores (antibiotic treatment, specialist medical visits).

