### Participant timeline {13}

Patients will be screened for eligibility criteria. Consent will be obtained from the patients, if possible, or their legal representative. Thereafter, patients will be randomized into the treatment or control group. After randomization, the skin underneath the mask and the auricle and occipital regions will be inspected to check for any possible pressure sores every 12 h for the following 4 days. Patient status at hospital discharge will also be evaluated (Fig. 2).

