## Statistical methods

### Statistical methods for primary and secondary outcomes {20a}

The analysis will be performed according to the intention-to-treat (ITT) principle. Descriptive statistics will be calculated to summarize patient characteristics collected at study entry according to the randomization group. Categorical variables will be reported as absolute frequencies and percentages. Continuous variables will be represented as mean and standard deviation or median first and third quartiles if not normally distributed according to the Shapiro–Wilk test.

The raw risk of pressure sore will be calculated at each time point as the ratio between the number of subjects who developed a pressure sore at a given time point divided by the number of subjects undergoing NIV at that time point. Patients having a planned break at the time point considered, but not weaned off NIV, will be considered as patients undergoing NIV.

Mixed effect logistic regression models will be used to estimate the risk of pressure sores and the difference between interfaces, including a random intercept to account for clustering of the subjects within the center and repeated measures within patients. The response variable will be the presence/absence of pressure sores, whereas the independent variables will be the treatment, time (12, 24, 36, 48, 60, 72, 84, 96 h), and their interaction. The marginal predicted probabilities estimated by the model will provide the incidence of pressure sores at different times as well as overall. The inclusion of time as a covariate will allow to test the presence of a time trend in the incidence of pressure sores and to investigate the variation of time trends according to treatment group.

If the descriptive statistics will detect unbalanced characteristics between randomization groups (e.g., indication for NIV), the corresponding variables will be added as covariates in the logistic regression model.

Regarding the number of pressure sores, different mixed effect Poisson regression models will be applied: one for each time point to estimate the average number of pressure sores at each time point and a model in which only the highest number of pressure sores will be considered for each patient. Time will be included as offset to evaluate the average number of pressure sores per day.

The grade and location of pressure sores will be summarized using descriptive statistics at each time point.

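### The baseline skin exclusion matches neither the scored sites nor the outcome clock, and no listed baseline item records skin status, so a lesion present at randomisation can count as a primary event

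*Protocol article*

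**What the plan says.** **Who is kept out.** The Exclusion criteria remove "Patients, on admission, with skin breakdown or non-blanchable erythema in one of the following areas: nasal bridge, nasolabial fold, cheek, or scalp". They also remove patients with "More than 2 h of NIV application before randomization", so up to 2 h of NIV may precede randomisation.

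**Where sores are scored.** Outcomes {12} lists the recorded locations as "forehead, nose bridge, left cheek, right cheek, chin, left periauricular, right periauricular, and occipital". Participant timeline {13} says that, after randomisation, "the skin underneath the mask and the auricle and occipital regions will be inspected to check for any possible pressure sores every 12 h".

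**What counts.** The abstract states: "The primary outcome is the proportion of patients developing new pressure sores at 36 h from randomization". Objectives {7} also refers to new sores. Outcomes {12} defines the primary outcome as "the proportion of patients developing at least one pressure sore of any stage at 36 h from randomization", with no limit on site. The lowest stage, in Table 1 under Intervention description {11a}, is "A reddened, painful area on the skin that does not turn white when pressed".

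**What is modelled.** Statistical methods {20a} states: "The response variable will be the presence/absence of pressure sores".

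**What is recorded at baseline.** Plans for assessment and collection of outcomes {18a} describes ten database sheets: one for baseline, eight for the 12 to 96 h time points and one for discharge. The baseline variables include the Braden scale and home NIV or CPAP use, but no skin examination.

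**The concern.** The trial asks whether rotating interfaces prevents sores that arise after randomisation. To answer that, either every patient must be clear at every scored site at time zero, or the lesions present at time zero must be known so that they can be set aside. The eligibility rule secures the first only for some sites, and only at admission. Nothing in the listed data secures the second.

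The lowest countable stage is non-blanching redness, the same sign that the exclusion uses at its own sites. A mild mark at an uncovered site is therefore enough to make a patient an event at the first inspection. Allocation cannot have caused or prevented such an event. It adds to both arms, shrinks the risk difference and costs power. A later analysis plan could not recover a time-zero record that was never collected.

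**Working it through.** **1. Sites side by side.**

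| Scored site (Outcomes {12}) | Covered by the exclusion? |
|---|---|
| Nose bridge | Yes |
| Left cheek, right cheek | Yes |
| Occipital | Yes, if scalp is read to include it |
| Forehead | No |
| Chin | No |
| Left and right periauricular | No |

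On the generous reading of scalp, four of the eight scored sites have no counterpart in the exclusion.

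**2. Timing.** The exclusion is judged on admission; the outcome runs from randomisation. Indications (iii) and (iv) in the Inclusion criteria concern avoiding or preventing reintubation, so these patients may have been intubated between admission and randomisation. For indications (i) and (ii), NIV before randomisation is capped at 2 h. Background {6a} reports exposure times to ulcer on oronasal masks that start at 1.25 h but average 28.4 h, so lesions inside that window are possible but should be few.

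**3. Can later steps remove an old lesion?** The word *new* appears in the abstract and in Objectives {7}. It needs a reference examination, and none is listed among the baseline variables. The model then takes presence or absence of sores.

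**4. Reproducing the planned sample size.** Inputs from Sample size {14}: type I error 0.05 (taken as two-sided, since the section does not say), power 0.80, 23% versus 13%, dropout 5%.

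- Unpooled variance: n = (1.960 + 0.842)² × (0.23×0.77 + 0.13×0.87) / 0.10² = 228; 228/0.95 = 240.
- Pooled variance: n = 231; 231/0.95 gives 244.

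The stated 239 per group is reproduced to within 1 patient (unpooled) or 5 (pooled). Evaluable per arm: 239 × 0.95 = 227.

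**5. Dilution.** Let q be the share of each arm that enters with a lesion that is then counted. The observed risk is q + (1 − q)p, so the risk difference becomes (1 − q) × 10 points. With n = 227 per arm and p̄ the mean of the two observed risks p₁ and p₂:

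Power = Φ{ [ (p₁ − p₂)√n − 1.960 √(2p̄(1 − p̄)) ] / √(p₁(1 − p₁) + p₂(1 − p₂)) }

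For q = 0: [0.10 × 15.07 − 1.960 × 0.543] / 0.539 = 0.82, and Φ(0.82) = 0.794.

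| q (assumed) | Control | Rotation | Difference | Power | n per group for 80% power, with dropout (pooled) |
|---|---|---|---|---|---|
| 0 | 23.0% | 13.0% | 10.0 points | 0.794 | 244 |
| 1% | 23.8% | 13.9% | 9.9 points | 0.772 | 257 |
| 2% | 24.5% | 14.7% | 9.8 points | 0.750 | 271 |
| 5% | 26.9% | 17.4% | 9.5 points | 0.685 | 315 |
| 10% (stress case) | 30.7% | 21.7% | 9.0 points | 0.588 | 394 |

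No value of q is given in the document.

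**The case against.** **The outcome is worded as incident.** The abstract and objective say new, and Outcomes {12} speaks of patients developing a sore. A lesion known to be old would not meet that wording. This stands as evidence of intent. It does not supply the examination needed to apply the intent, and the model's response is worded as presence or absence.

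**A reader might infer that nobody looks at the skin at baseline.** The documents do not support that. The exclusion itself requires a look at some sites, it does not say that other sites go unexamined, and the schedule figure (Fig. 2) is not shown and may include a baseline check. Pre-existing erythematous skin disorders are also excluded. What can be said is narrower: the described baseline variables hold no skin status. Even if Fig. 2 did schedule a check, the exclusion sites and the model response would remain as written.

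**A reader might extend the timing gap to the whole trial.** Admission may mean admission to the treating unit, which narrows the gap. With NIV before randomisation capped at 2 h, the timing point bears mainly on post-extubation patients, whose share is not given.

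**A reader might infer bias in favour of one strategy.** Lesions present before randomisation are balanced in expectation, so dilution is the expected harm.

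**The magnitude has no anchor.** This is correct. A value of 10% at entry would be nearly half of the 23% control risk expected at 36 h and should be read only as a stress case. At 1% to 2% the loss is small.

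**Conclusion.** The mismatch is in the text. Four scored sites lie outside the exclusion, the exclusion is tied to admission and not to randomisation, and nothing in the listed baseline data lets *new* be applied. Following the plan as written, a lesion present at randomisation can be counted as a primary event at the forehead, chin or either periauricular area. In patients randomised well after admission, it can be counted at any site.

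The consequence is non-differential dilution. Power moves from 0.79 to 0.77, 0.75 or 0.69 if 1%, 2% or 5% of each arm is affected. These figures assume equal prevalence in both arms, a two-sided 5% test, 227 evaluable patients per arm, and that the planned 23% and 13% do not already include such lesions. The definitional gap does not depend on the prevalence; its practical weight does, and may be modest.

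**What to change.** Inspect all eight scored sites at randomisation, before the allocated strategy starts, and record the status of each on the baseline sheet. Define the primary event, and the model response with it, as a sore at a site that was clear at that inspection. Location is already recorded at every time point, so the outcome sheets need no change. Widening the exclusion to all scored sites at randomisation is an alternative, not an additional step: if every patient is clear at entry, the event rule has nothing left to do.

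The cost is one baseline case report form item and a short inspection that extends the existing eligibility check. It also requires a formal amendment, which must be approved by the review board of each participating centre (23 centres are named in Study setting {9}). Recruitment began in December 2022, so earlier is better.

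For patients already enrolled without a baseline record, report a sensitivity analysis restricted to the sites covered by the exclusion criterion. That closes the site gap for them but not the timing gap, and the report should say so.
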